### Randomisation

#### Procedure

After receiving signed informed consent from a participant at the first clinic appointment (two week pre-quit), the study nurse will telephone the participant to ensure participation and commitment to the quit attempt. If confirmed, the trial co-ordination team (KCL) will send the participant's data that are required for randomisation to the statistical team (Cambridge), and receive back the identity of the allocated group.

#### Method

Each participant will be randomised to one of the two arms on a 1:1 basis. The randomisation will be stratified by nurse, cigarettes smoked per day (i.e., 10-14 or 15+) and the Fagerström Test for Nicotine Dependence score (< 7 (< 8) or 7-10 (8-10)). Within each stratum, a randomisation sequence will be generated using blocking, with successive randomly selected blocks sizes of six, eight and ten, in order to minimise predictability of assignment. Families will be allocated as clusters to the same arm to avoid contamination and reflect practice. First participants from families will be assigned a group according to the next blocked allocation in their stratum.

#### Concealment

At the start of the trial the randomisation sequence in each stratum will be generated using randomly permuted blocks by the trial statistician and concealed from the trial coordination team, therapists and participants. The statistical team will be given a participant's study identification code and the stratifier data necessary for the participant's randomisation. The only other information sent will be the participant's date of birth which will allow, at study closure, the agreement between the sequence generated and that used in the trial to be confirmed to have been securely operated.

After assignment, participants' study arm will not be concealed from participant, nurse or researchers. This will include the nurses collecting the primary endpoint data as they are also delivering the intervention. However, group allocation will be concealed from the research team collecting secondary outcome data on self-reported smoking status.

### Fidelity checks

All sessions in which the rationale for the prescription will be presented (*ie *the second session, one-week pre-quit) will be tape-recorded. During the recruitment phase of the trial, assessments of a subsample of randomly selected recordings will be conducted to assess the fidelity of intervention delivery. Subsequently, feedback will be provided to the nurses to optimise intervention delivery. In addition, a sub-sample of these recordings will be randomly selected and transcribed to assess fidelity to the clinical protocol. The tapes will be stored in a locked cabinet until the end of the trial and completion of this analysis. They will be accessible only to the study team.

### Adverse events monitoring

At each of the weekly clinic visits following the quit attempt, participants will complete a schedule of nicotine overdose symptoms. This assessment is recorded in the Case Report Form, together with details of any action taken (e.g. continuing with prescribed dose/directing the participant to a lower dose). In addition, at each weekly clinic visit, participants will be asked about the occurrence of any significant side effects from their treatment. The trial nurses will enquire about any adverse events to determine their severity and provide appropriate advice about their management (e.g. rotating the NRT patch site or use of emollients for skin reactions). Examples of adverse events include symptoms of nicotine overdose (e.g. vomiting, headaches) and adverse reactions to NRT (e.g. skin and subcutaneous tissue disorders). All of these events as well as all comments made by participants and health care professionals will be logged in the Trial Log File. Each event will be given an individual number and logged in a computer database. Any follow-up or further action needed will also be logged. No personal information will be included unless absolutely necessary. The Trial Log File will be stored in a locked office.

Any incident judged to be serious by the principal investigator and the research team will be reported to the trials independent Data Monitoring Committee within 24 hours. Any serious adverse events will be reported to Medicines and Healthcare Products Regulatory Authority (MHRA).

### Research Governance

This study is classified as a Clinical Trial of an Investigational Medicinal Product (CTIMP) as it investigates the efficacy of a medicine for which the prescribed dose is determined by the results of genetic testing. Although the trial participants may be prescribed NRT without participating in the trial, the dosage and timing of the prescription is determined by a clinical protocol and therefore the Medicines for Human Use (Clinical Trials) Regulations (2004), apply. Further information is available from the MHRA algorithm at http://www.ct-toolkit.ac.uk. MHRA approval has been granted (MHRA ref: 24570/0002/001-0001; Eudract no: 2006-000106-24).

Ethical approval for the trial has been granted (Hertfordshire 1 Research Ethics Committee, ref: 06/Q0201/21, approved 26^th ^June, 2006). R&D approval has been granted from the relevant PCTs in Birmingham and Bristol where the interventions will take place.

### Statistical Analysis

All analyses will be primarily on an intention-to treat-basis, with the intention to treat population defined as those randomised into the trial. This compares the pragmatic policies represented by the two intervention arms amongst all those eligible and consenting. This will be supported by an explanatory per protocol analysis, with the per protocol population defined as all participants with the exclusion of those who chose not to attend to receive their allocated intervention.

#### Hypothesis I: Analysis of primary outcome

For the analysis of the primary outcome, the proportion of all NRT consumed in the first 28 days of quitting will be compared between arms using an independent samples t-test and by estimating the 95% confidence interval for the observed between-arm difference in mean of proportion of NRT consumed (Hypothesis I). This will be confirmed using the nonparametric Bootstrap BCA method for estimating the difference between two means with confidence interval.

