### Sample size calculation

With 315 participants per arm, there is 90% power to detect a 7.5% difference in the mean proportion of NRT consumed using a two-tailed test at the 5% level of significance. This is equivalent to detecting approximately a two days' worth difference in mean NRT consumption over a 28-day period. The calculation is based on the skewed distribution of days of prescribed NRT patch use reported by Alterman and colleagues [41] where 55% of participants reported high use and the remainder had a uniformly spread distribution of use. Assuming the same mixed distribution, with 50% and 65% of high-use participants and the remainder uniformly distributed in the two arms, the implied difference in mean consumption was 7.5%. By repeated random sampling, the distribution of the mean within each group was close to normal. The estimated pooled within-group standard error was 1.85%, and both Mann-Whitney and unpaired t-tests provided at least 90% power.

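### The primary t-test uses neither the stratification factors nor the family clusters of the randomisation; the errors are modest, partly cancel, and are cheap to remove

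*Protocol article*

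**What the plan says.** In the Protocol article, the Method part of Randomisation sets two restrictions on allocation. First, "The randomisation will be stratified by nurse, cigarettes smoked per day", and also by Fagerström score (FTND), with permuted blocks inside each stratum. The FTND cut-off moved from 7 to 8 after an interim look at prescribing. Second, "Families will be allocated as clusters to the same arm to avoid contamination and reflect practice"; only the first member of a family takes the next allocation in a stratum.

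The section Hypothesis I: Analysis of primary outcome fixes the test. Adherence over 28 days "will be compared between arms using an independent samples t-test and by estimating the 95% confidence interval for the observed between-arm difference" in mean proportion consumed. It adds: "This will be confirmed using the nonparametric Bootstrap BCA method for estimating the difference between two means with confidence interval". Neither sentence mentions strata or families. Nurse enters a model only under Subgroup analyses, in the interaction test. The Sample size calculation makes no allowance for families.

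**The concern.** An analysis should reflect the way allocation was restricted. When arms are balanced within strata that predict the outcome, the difference in means varies less from one randomisation to another than the two-sample formula assumes. The reported standard error is then too large and precision is lost. When relatives share an arm and behave alike, the difference varies more than the formula assumes, and the standard error is too small. The two-sample bootstrap as described shares both faults, because it mentions neither strata nor family-level resampling.

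The protocol itself gives reason to expect the stratifiers to predict adherence. Cigarettes per day sets the patch dose and FTND sets the oral dose in the phenotype arm, and both doses enter the denominator of the outcome. Design considerations allows that people may take a smaller share of a larger dose. The nurses deliver the intervention and also collect the primary endpoint. What is at stake is the precision and exact calibration of the headline interval.

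**Working it through.** **Inputs from the documents (Sample size calculation).** 315 per arm, a 7.5-point difference, two-sided 5%, 90% power claimed. The assumed distribution has 50% and 65% high users, the rest uniform. The within-group standard error is 1.85%.

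**Inputs the documents do not give, assumed here.** R², the share of outcome variance explained by the strata: 5% to 10% (2% to 10% in step 4). f, the share of participants in two-person families: 2% to 20%. ICC, the within-family correlation: 0.1 to 0.5.

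**1. The plan's own figure.** Read high use as 100% and the rest as uniform on 0 to 1.
- Means: 0.50 + 0.50/2 = 0.750 and 0.65 + 0.35/2 = 0.825. The difference is 0.075, as stated.
- Variances: 0.50 + 0.50/3 − 0.750² = 0.1042 and 0.65 + 0.35/3 − 0.825² = 0.0860. Pooled SD = √0.0951 = 0.308.
- SE of the difference = 0.3084 × √(2/315) = 2.457 points.
- Power = Φ(7.5/2.457 − 1.96) = Φ(1.092) = 86.3%. Simulation of this mixture (8,000 runs) gave 85.6% for the t-test and 95.2% for Mann-Whitney.
- From the stated standard error instead, SD = 1.85% × √315 = 32.8% and power is 81.8%.

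The stated 90% is therefore not reproduced for the t-test. That is a separate matter; 86.3% serves here only as the starting value.

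**2. Strata ignored.** The true SE is 2.457 × √(1 − R²). Size of the unadjusted test = 2[1 − Φ(1.96/√(1 − R²))]. Power with adjustment = Φ(7.5/(2.457√(1 − R²)) − 1.96).

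| R² (assumed) | True SE | Size, unadjusted | Coverage | Power, adjusted |
|---|---|---|---|---|
| 5% | 2.395 | 4.4% | 95.6% | 87.9% |
| 10% | 2.331 | 3.9% | 96.1% | 89.6% |

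The 86.3% is the t-test's power by formula. Stratified allocation already gives the unadjusted test a little more: Φ((7.5 − 1.96 × 2.457)/true SE) = 86.9% at R² = 5% and 87.5% at 10%. Measured that way, adjustment adds about 1 to 2 points.

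**3. Families ignored.** For pairs, design effect DE = 1 + f × ICC, and size = 2[1 − Φ(1.96/√DE)].

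| f, ICC (assumed) | DE | Type I error |
|---|---|---|
| 2%, 0.1 | 1.002 | 5.0% |
| 10%, 0.3 | 1.03 | 5.3% |
| 20%, 0.5 | 1.10 | 6.2% |

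**4. Both together.** Replace DE by k = (1 − R²)(1 + f × ICC). The combinations tried were R² of 2%, 5% and 10% with f/ICC of 5%/0.3, 10%/0.3 and 20%/0.5.
- Lowest: k = 0.90 × 1.015 = 0.9135, size 4.0%.
- Highest: k = 0.98 × 1.10 = 1.078, size 5.9%.
- In between, for example: k = 0.95 × 1.03 = 0.9785, size 4.8%.

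**The case against.** The strongest reply is that this is refinement, not error. Every magnitude is assumed. The strata part concerns efficiency: an unadjusted test after stratified randomisation is conservative, and the raw difference in means is transparent and matches the tests used for the sample size. The family part may be negligible, since recruitment is by letter to smokers on practice lists and nothing suggests that many relatives enrol. The article is also condensed, and covariate adjustment is often left to a statistical analysis plan.

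Most of this stands as a limit on size. It does not remove the point, because the article names its primary test, and that test assumes an independence that the family rule breaks by design. What an unseen plan may add to supporting analyses cannot be inferred either way.

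Three stronger readings are tempting and not supported. A reader might infer that the type I error is inflated; that holds only if the family effect outweighs the strata effect, and the documents cannot show it. A reader might blame the shortfall from 90% power on the missing adjustment; the shortfall arises in the sample size section and would exist without strata or families. A reader might infer bias because later relatives join with an arm already fixed and possibly known. That is a question of selection at entry, which stratum terms and clustered standard errors do not address.

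**Conclusion.** The mismatch between the randomisation and the primary analysis is explicit, and nothing else in the article repairs it. Its effect is small to moderate. Strata explaining 5% to 10% of variance give a size of 4.4% to 3.9% and some lost precision. Families give 5.0% to 6.2%, which is minor unless many relatives take part. Combined size is about 4.0% to 5.9% over the combinations tried, with net direction unknown. All of these rest on assumed R², family share and ICC; the power figures also rest on reading high use as full use. The plan should be changed because the correction is nearly free and still targets a difference in mean adherence, not because the planned test would mislead.

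**What to change.** Make the primary estimate, with its 95% interval and test, the arm coefficient from a linear model of 28-day adherence on arm, nurse, cigarettes-per-day group and FTND group, with family-clustered robust standard errors. Use each participant's own baseline values and the FTND cut-off in force at entry. This defines the covariates for later family members too, who inherit an arm but may belong to a different stratum from the first.

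Run the BCa bootstrap by resampling whole families within arm, counting a single participant as a family of one, and refit the same model each time. Resampling families within strata would not be well defined, because a family can straddle strata.

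Keep the simple t-test as a supporting analysis. Add a sensitivity analysis restricted to the first-randomised member of each family.

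The cost is a few sentences of analysis wording and some code. The stratifiers and family membership are already needed to randomise. The drawback is a slightly less simple headline test.

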#### Secondary analyses

The proportion of all NRT consumed in the first seven days of quitting will be compared as described for the primary outcome. Measures of abstinence will be analysed between arms as the difference in proportions with 95% confidence interval and chi-squared test.

#### Hypothesis II: within-subgroup outcome

Amongst those classified as not abstinent at the six month follow-up, as judged by 7-day point prevalence abstinence, an independent-samples t-test will be used to compare motivation to make another quit attempt between arms.

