We predict that prescribing tailored to genotype increases adherence to NRT compared with prescribing tailored to phenotype, by strengthening the perceived effectiveness of the medication, a good predictor of adherence [25]. Consumption of NRT directly increases the likelihood of sustained smoking cessation; this being dose-dependent in that the more NRT consumed, the greater the chance of sustained cessation [26,27]. It is the most popular medication used in UK NHS clinics [28].

Furthermore, given the common representation of genes as deterministic, conferring immutable effects, it is important to document the impact of DNA testing for nicotine responsiveness in the longer term upon attributions for failure to quit smoking among those smokers who do not quit. Informing patients that their prescription is tailored to their genotype may have negative effects through engendering a sense of fatalism, which is associated with perceiving a genetic cause to a health problem [29]. Such fatalistic responses are predicted to result in reduced motivation in this group to make a future quit attempt (amongst those who fail to quit by six months).

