### Objective and hypotheses

We will estimate the impact upon adherence to NRT of informing smokers that their oral dose of NRT has been tailored on the basis of DNA analysis.

The trial tests two hypotheses:

I	Adherence to NRT is greater among smokers who are informed their oral dose of NRT is tailored to an analysis of DNA (genotype), compared to one tailored to nicotine dependence (phenotype).

II Amongst smokers who fail to quit at six months, motivation to make another quit attempt is lower when informed that their oral dose of NRT was tailored to genotype rather than phenotype.

While the trial is not powered to assess long term behavioural outcomes related to smoking, prolonged abstinence is measured at six months post quit date.

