#### Hypothesis II

##### i) Within-subgroup outcome: Motivation to make another quit attempt

The sub-group comprises those participants who fail to achieve prolonged abstinence at the six month follow-up. The primary outcome within this subgroup is motivation to stop smoking in the next four weeks.

This is measured using the mean score of the following four items measured using 7-point bipolar scales: "Do you intend to stop smoking in the next 4 weeks?"[response scale labelled at each end: "definitely do not" (1) and "definitely do" (7)]: "How likely is it that you will stop smoking in the next 4 weeks?" ["very unlikely" (1), and "very likely" (7)]; "How determined are you to stop smoking in the next 4 weeks?" ["not at all" (1), and "extremely" (7)]; and "How much do you want to stop smoking in the next 4 weeks?" ["not at all" (1), to "very much" (7)].

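### Hypothesis II is tested by an unadjusted t-test in a group formed after randomisation by abstinence, so randomisation does not protect it and the intention-to-treat statement does not fit it

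*Protocol article*

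**What the plan says.** The prediction, under Objective and hypotheses, is that among smokers who have not quit by six months "motivation to make another quit attempt is lower when informed that their oral dose of NRT was tailored to genotype rather than phenotype".

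The analysis section for Hypothesis II sets the population as "Amongst those classified as not abstinent at the six month follow-up", with abstinence judged by seven-day point prevalence, and the method: "an independent-samples t-test will be used to compare motivation to make another quit attempt between arms". It names no covariates. The Outcomes section uses a different abstinence rule for the same subgroup: "The sub-group comprises those participants who fail to achieve prolonged abstinence at the six month follow-up". Under either rule, membership is decided at six months.

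The opening of Statistical Analysis states: "All analyses will be primarily on an intention-to treat-basis, with the intention to treat population defined as those randomised into the trial". It makes no exception for Hypothesis II.

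The Background links the intervention to the outcome that selects the group. Genotype tailoring is predicted to raise adherence, and "Consumption of NRT directly increases the likelihood of sustained smoking cessation", with a dose relation: "the more NRT consumed, the greater the chance of sustained cessation". The Background also says that prescribing by genetic test could undermine cessation by making willpower seem less important.

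**The concern.** Comparing arms only among those who failed conditions on something that happens after randomisation. If the genotype message leads more people to quit, and those extra quitters are the more motivated, their departure lowers mean motivation among the genotype-arm failures even if the message has no effect on anyone's motivation. A benefit on quitting would then appear partly as the predicted harm.

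Hypothesis II is one of the trial's two stated hypotheses and concerns a possible harm of genetic tailoring. A reader who takes the intention-to-treat statement at face value would give the result the standing of a randomised comparison, which it does not have.

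**Working it through.** **Plan's own figure.** The article gives no sample size, power, expected quit rate or arm difference in abstinence for Hypothesis II, so there is nothing to reproduce. The size of the bias has to be explored over assumptions.

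**Input from the document.** 315 participants per arm (Sample size calculation).

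**Assumptions.** Quit rates of 10% to 25%; liability to quit and motivation bivariate normal with correlation r of 0.2 to 0.5; no true effect of arm on motivation; all failures respond.

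**Formula.** With quit rate p and z_p the upper-p normal quantile, mean motivation among failures in SD units is −r·λ(p), where λ(p) = φ(z_p)/(1−p). If r is the same in both arms, the bias (genotype minus phenotype) is −r·[λ(p_G) − λ(p_P)].

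| p | z_p | φ(z_p) | λ(p) | Failures of 315 |
|---|---|---|---|---|
| 10% | 1.282 | 0.1755 | 0.1950 | 284 |
| 15% | 1.036 | 0.2332 | 0.2743 | 268 |
| 17% | 0.954 | 0.2531 | 0.3049 | 261 |
| 20% | 0.842 | 0.2800 | 0.3500 | 252 |
| 25% | 0.674 | 0.3178 | 0.4237 | 236 |

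**Bias with equal r in both arms.**

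| Phenotype v genotype quit rate | Difference in λ | r = 0.2 | r = 0.3 | r = 0.5 |
|---|---|---|---|---|
| 15% v 17% | 0.031 | −0.006 | −0.009 | −0.015 |
| 15% v 20% | 0.076 | −0.015 | −0.023 | −0.038 |
| 15% v 25% | 0.149 | −0.030 | −0.045 | −0.075 |
| 10% v 20% | 0.155 | −0.031 | −0.046 | −0.077 |

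Negative values favour Hypothesis II. With equal quit rates and equal r the bias is zero.

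**Scale.** The standard error is about √(2/n): √(2/284) = 0.084 and √(2/252) = 0.089 SD. The largest bias in the table is therefore just under one standard error. For comparison, 252 failures per arm give 80% power for (1.96 + 0.84) × 0.089 = 0.25 SD.

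**Direction.** Let r differ by arm at 15% v 20% quitting, so that the bias is −r_G × 0.3500 + r_P × 0.2743:
- r of 0.3 falling to 0.2 in the genotype arm: −0.0700 + 0.0823 = +0.012 SD
- r of 0.5 falling to 0.4: −0.1400 + 0.1372 = −0.003 SD
- r of 0.3 falling to 0: +0.082 SD

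Quitting rises in every case, yet the bias is against Hypothesis II in two of the three and close to nil in the other.

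**Check with a different model.** Quitting was made logistic in latent motivation (odds ratio 1.5 to 3 per SD), with six-month motivation correlated 0.5 to 0.9 with it and phenotype-arm abstinence of 10% or 20%. All of these are assumptions.

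| Abstinence gain in genotype arm | Bias (SD) | Two-sided error at nominal 5% |
|---|---|---|
| 0 | 0 | 5.0% |
| 2 points | −0.004 to −0.016 | 5.0% to 5.5% |
| 5 points | −0.010 to −0.040 | 5.1% to 7.8% |
| 10 points | −0.019 to −0.079 | 5.5% to 15.9% |

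In the same model, with 20% abstinence in the phenotype arm, an odds ratio of 2 and a correlation of 0.7, the sign reverses if genotype lowers abstinence by 5 points (+0.022 SD). It also reverses if the odds ratio falls from 2 to 1 in the genotype arm (+0.090 SD, error about 17%).

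**The case against.** The restriction to failures is open, pre-specified and part of the question. The subgroup is labelled as such, and asking abstainers whether they intend to stop in the next four weeks makes little sense. No participant is hidden or moved between arms. This stands: the conflict with the intention-to-treat statement is one of wording and interpretation, and the target population is legitimate. It does not make the two groups of failures comparable.

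A reader might infer that the test is necessarily biased towards the predicted result, or always so when the message helps people quit. The documents do not support that. Hypothesis I concerns adherence; abstinence lies downstream, and the article says the trial is not powered for long-term smoking outcomes. No abstinence gain is stated, and gains of 5 to 10 points are assumptions. The willpower route in the Background could weaken the link between motivation and quitting in the genotype arm, which reverses the sign.

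Two further objections have force. Adjustment for the stratifiers cannot remove selection that acts through motivation itself. And the planned report of the abstinence difference with its confidence interval already lets a reader judge one route to this bias, a change in how many quit. It does not show a change in which smokers quit. An unseen analysis plan may add covariates, but the article itself fixes an unadjusted t-test and an unqualified statement about all analyses.

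**Conclusion.** The point holds in conditional form. The Hypothesis II comparison is not protected by randomisation, is planned without adjustment, and does not fit the statement that all analyses use everyone randomised. It can be biased, and the direction depends on whether, and among whom, the genotype message changes quitting.

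Under the assumed rates and correlations, with quitting linked to motivation equally in both arms, the bias is about 0.01 to 0.04 SD for a 2 to 5 point abstinence gain and up to about 0.08 SD for 10 points, against a standard error of about 0.09 SD. It is small unless the effect on abstinence is large or the arms differ in how strongly motivation drives quitting. The difference between the two abstinence rules for the subgroup is a separate matter; this point holds under either.

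**What to change.** 1. In the Hypothesis II analysis, replace the t-test by a linear regression of motivation on arm, adjusted for the randomisation stratifiers already collected (FTND, cigarettes per day and nurse), plus baseline motivation if it was recorded.
2. In the opening of Statistical Analysis, exempt Hypothesis II from the intention-to-treat statement. Describe it as a non-randomised comparison among those who failed to quit, to be read beside the between-arm abstinence difference planned under Secondary analyses.
3. State that adjustment reduces the selection bias but does not remove it.
4. If wanted, add an all-randomised composite, with validated quitters ranked most favourably and failures ranked by motivation, as a supportive sensitivity analysis only. It should not be a condition for concluding harm: it answers a broader question and could hide a real effect among failures whenever genotype tailoring improves quitting.

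The cost is wording and analysis only, with no new data. The adjusted estimate is slightly less simple to present, and it should gain some precision.

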#### Data collection

Participants will be asked to attend seven weekly clinic sessions. In the first clinic participants will complete a baseline questionnaire. NRT will be prescribed according to the protocol at the second clinic visit and a quit date agreed. All participants will be given a small card summarising their top up dose of NRT and describing the rationale for this, which will vary according to whether it is tailored by DNA analysis or nicotine dependence. In the third clinic a second questionnaire will be completed. Participants are requested to continue to take their NRT as prescribed for four weeks post quit attempt and to attend weekly clinic visits. All participants will be contacted six months after their quit dates to assess the study endpoints by questionnaires sent by post or administered by telephone.

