##### Validated abstinence from smoking at 28 days and six months

At six months, 7-day point prevalence and six month prolonged abstinence will be recorded. Point prevalent abstinence is defined as smoking not more than 5 cigarettes for the seven days prior to the assessment confirmed by salivary cotinine < 15 ng/ml. Prolonged abstinence (defined as sustained abstinence after an initial two week grace period as recommended by Hughes and colleagues [39] will be operationalised by: a) self-reported consumption of not more than five cigarettes since the quit date; and b) salivary cotinine levels of less that 15 ng/ml [40]. A 28-day abstinence measure will also be reported, with validation by carbon monoxide less than 10 ppm, with backward inference of missing data from the 6 month measure following Russell standard criteria [40].

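### Hypothesis II concerns smokers who did not manage to stop, but its analysis set is everyone without cotinine-confirmed abstinence, which as written includes unconfirmed self-reported quitters

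*Protocol article*

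**What the plan says.** All references are to the protocol article.

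- **Hypothesis** (Objective and hypotheses): the population of Hypothesis II is smokers whose attempt has failed by six months. The prediction is lower motivation to try again in the genotype arm.
- **Subgroup in the Outcomes section** (Within-subgroup outcome): "The sub-group comprises those participants who fail to achieve prolonged abstinence at the six month follow-up".
- **Subgroup in the Statistical Analysis section** (Hypothesis II: within-subgroup outcome): "Amongst those classified as not abstinent at the six month follow-up, as judged by 7-day point prevalence abstinence". The arms are compared by an independent-samples t-test.
- **Definitions** (Validated abstinence from smoking at 28 days and six months): point prevalence is "smoking not more than 5 cigarettes for the seven days prior to the assessment confirmed by salivary cotinine < 15 ng/ml". Prolonged abstinence needs no more than five cigarettes since the quit date and also "b) salivary cotinine levels of less that 15 ng/ml".
- **Outcome**: the mean of four items scored 1 to 7, all about the coming four weeks. The first asks "Do you intend to stop smoking in the next 4 weeks".
- **Six-month contact** (Data collection): participants are contacted "to assess the study endpoints by questionnaires sent by post or administered by telephone".

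The only missing-data rule for abstinence in the article covers the 28-day measure. The section on missing data covers the primary outcome only.

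**The concern.** Requiring biochemical confirmation is a sound, conservative convention when the endpoint is an abstinence rate. Here its complement is used for something else: to decide whose motivation score is analysed. A person can fail the confirmed definition because they smoke, or because they report not smoking and have no confirming sample. Hypothesis II is about the first kind only. The second kind has no natural answer to a question about intending to stop, and may answer near the top of the scale or leave the items blank.

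Those who answer make each arm's mean partly a measure of how many unconfirmed abstainers it holds. If the arms differ in that share, a difference in motivation appears or disappears for a reason unrelated to the fatalism the hypothesis is meant to detect. If the shares are equal, a true difference among smokers is diluted.

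**Working it through.** The plan gives no figure for the Hypothesis II subgroup; its sample size calculation concerns NRT consumption only. The check is therefore a reading of the definitions, followed by an illustration under stated assumptions.

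**1. Definitions side by side**

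| Place | Criterion whose failure defines the set | Self-report part | Cotinine part |
|---|---|---|---|
| Outcomes section | Prolonged abstinence | at most 5 cigarettes since quit date | below 15 ng/ml |
| Statistical Analysis section | 7-day point prevalence | at most 5 cigarettes in last 7 days | below 15 ng/ml |

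Two things follow.

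- Under either row, someone who meets the self-report part but not the cotinine part is outside the abstinent group, so by the letter inside the Hypothesis II set.
- The two sets differ. Anyone with at most five cigarettes since the quit date also has at most five in the last seven days, so the Statistical Analysis set lies within the Outcomes set. The Outcomes set also holds people who smoked earlier in follow-up but are now confirmed point-prevalent abstainers. This contradiction is in the text and needs no assumption.

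**2. How many people could be involved**

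Assumptions, none of them in the article: self-reported abstinence s = 20-30%; unconfirmed fraction of those u = 20-40%; all 630 participants followed up and answering the items.

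- Unconfirmed abstainers = 630 × s × u
- Share of the set f = s × u / (1 − s(1 − u))

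| s | u | People | Share f |
|---|---|---|---|
| 0.20 | 0.20 | 630 × 0.04 = 25 | 0.04/0.84 = 4.8% |
| 0.20 | 0.40 | 630 × 0.08 = 50 | 0.08/0.88 = 9.1% |
| 0.30 | 0.20 | 630 × 0.06 = 38 | 0.06/0.76 = 7.9% |
| 0.30 | 0.40 | 630 × 0.12 = 76 | 0.12/0.82 = 14.6% |

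With lower assumed rates (s = 10-25%, u = 10-30%) the same formulas give about 6 to 47 people, or 1% to 9% of the set.

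**3. Effect on the contrast**

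Shift = (difference in f between arms) × (mean of unconfirmed abstainers − mean of smokers). Assume means of 7 and 4.5, a gap of 2.5, and the same u in both arms. Let one arm have s = 20% and the other s = 30%.

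- u = 0.20: 7.9% − 4.8% = 3.1 points; 0.031 × 2.5 = 0.08 scale points
- u = 0.40: 14.6% − 9.1% = 5.5 points; 0.055 × 2.5 = 0.14 scale points

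These figures need a full ten-point arm difference in self-reported abstinence. With 20% against 25%, f at s = 25% is 0.05/0.80 = 6.3% or 0.10/0.85 = 11.8%. The differences are 1.5 and 2.7 points and the shifts 0.04 and 0.07. With equal shares there is no shift. If unconfirmed abstainers then score alike in both arms, a true difference among smokers is multiplied by 1 − f, that is by 0.95 down to 0.85.

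**The case against.** The strongest reply is that the article does not say what happens when the six-month saliva sample is absent. Such a person could be classed as not abstinent or as having unknown status, and a condensed article may leave that rule to the full protocol or the analysis plan. A reader might infer that the plan counts unverified people as smokers; no text says so. This stands, and it makes the point conditional. It does not remove it, because the stated set selects on confirmation while the hypothesis and the items call for selection on current smoking.

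Other parts of the reply also stand:

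- The article does not say whether self-reported quitters are given the motivation items. The analysis paragraph fixes who is analysed, not who is asked. Those who leave the items blank do not affect the t-test.
- Postal or telephone contact makes a questionnaire without a sample possible, but the article does not describe saliva collection or give a return rate.
- A reader might infer that the predicted fall in motivation would be masked, because genotype tailoring is expected to raise adherence and so cessation. The article does not settle this. Its Background also says that genetic prescribing could undermine cessation by making willpower seem less important, and the trial is not powered for long-term smoking outcomes.
- A reader might infer a larger distortion. Within the ranges of 20-30% and 20-40%, and with the same unconfirmed fraction in both arms, the share difference cannot exceed about 5.5 points. A larger one needs sample return to differ by arm, for which the article gives no ground.
- Replacing a verified definition with a self-reported one is a trade-off, since people who misreport abstinence leave the main analysis.

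**Conclusion.** The point holds conditionally. As defined, and unless a rule elsewhere says otherwise, the Hypothesis II set includes people who report having stopped but are not confirmed, and any who answer the items contaminate the arm means. The mismatch with the hypothesis and the items is in the text. Its size and direction are not.

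Under the main assumptions above, unconfirmed abstainers are about 5-15% of the set. A 3-5.5 point arm difference in share shifts the contrast by about 0.08-0.14 points on a 1-7 scale, and less if the arms are closer. The article gives neither a standard deviation nor a target difference for motivation, so whether that is material cannot be judged from it. The documents do not support calling Hypothesis II biased in a known direction.

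Separately and without condition, the Outcomes and Statistical Analysis sections define the subgroup by different criteria and must be reconciled. Because this is one of the trial's two hypotheses and the change is small, it is worth making.

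**What to change.** Use one Hypothesis II population in both the Outcomes and the Statistical Analysis sections: participants who themselves report smoking at the six-month contact beyond the five-cigarette allowance. The seven-day form of that allowance fits best, because the items presuppose current smoking; the other form counts from the quit date.

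- State that an absent or unconfirming cotinine result does not place a self-reported non-smoker in this population.
- Keep cotinine verification for the abstinence endpoints as they stand.
- Report the number of unverified self-reported abstainers in each arm, and how many of them answered the motivation items.
- Add a sensitivity analysis that includes them.

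The cost is about one sentence in each of the two sections and one extra analysis. The downside is a slightly smaller set, with people who misreport abstinence left out of the main analysis; the sensitivity analysis shows how much that matters.
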